# The effectiveness of a behavioral science and design intervention for family savings on use of maternal health services and male involvement: study protocol for a randomized controlled trial

**DOI:** 10.1186/s12889-022-13985-1

**Published:** 2022-08-19

**Keywords:** Maternal health, Male involvement, Savings, Mobile money, Behavioral science

## Abstract

**Background:**

Lack of financial preparedness for pregnancy can lead to adverse outcomes during childbirth. Behavioral science interventions have been shown to influence savings behavior. Financial savings interventions can be adapted for the purpose of encouraging individuals to save towards maternal healthcare costs. This article describes a protocol to assess the effectiveness of an intervention formulated with a behavioral science approach for encouraging use of maternal health services through increased financial savings for birth preparedness and maternal healthcare costs among pregnant women or their partners in Uganda.

**Methods:**

A randomized controlled trial will be conducted to assess the effectiveness of the intervention among pregnant women or their partners in Uganda’s central region, including the capital of Kampala. Seven hundred pregnant women (12–35 gestational weeks) or their partners will be recruited. All participants will receive access to a committed mobile money health savings account provided by a local organization that also offers savings targets and reminders for antenatal care appointments and health tips as part of a “Mamas Program” offered to expectant mothers. The time period in the intervention is from the day of enrollment until two weeks after the delivery date. The control group will receive the standard Mama Program offering. The intervention group will receive the standard Mama Program offering plus behavioral designs encouraging savings behavior through short-message service (SMS) text messages. The primary outcome is usage of maternal health services measured by level of birth preparedness and delivery at a health facility. Secondary outcomes include male involvement in maternal healthcare, measured by financial support, as well as total savings for healthcare, assessed using the validated amount of savings accrued in participants’ clinicPesa accounts from the day of enrollment plus any withdrawals for healthcare expenditures during the intervention period.

**Discussion:**

The study will contribute to a better understanding of the effectiveness of behavioral designs encouraging financial savings during pregnancy into committed mobile money health savings accounts. The study could contribute to demonstrating the effectiveness of savings on birth preparedness, usage of maternal health services, and male involvement in maternal healthcare.

**Trial registration:**

UMIN-CTR Clinical Trial, UMIN000046472. Registered on 19 January 2022. https://center6.umin.ac.jp/cgi-open-bin/icdr_e/ctr_view.cgi?recptno=R000053008

**Supplementary Information:**

The online version contains supplementary material available at 10.1186/s12889-022-13985-1.

## Background

Maternal mortality is a common problem worldwide despite high levels of investment and effort over the last several decades, especially in low and middle-income countries [1]. The first target under Sustainable Development Goal 3, “Good Health and Well-being,” is to reduce the global maternal mortality ratio (MMR) to less than 70 per 100,000 births, indicating its importance for development and progress towards attaining universal health coverage and human rights through health [2]. MMR is 211 per 100,000 live births worldwide, and sub-Saharan Africa (SSA) carries two-thirds of the global burden of MMR [1].

Thaddeus and Maine developed the “Three Delays Model,” which describes the three main factors that affect a mother’s decision to seek treatment for delivery: 1) delaying to seek care, 2) delaying arrival at a health facility, and 3) delaying the provision of adequate care [3]. Educational attainment, a well-functioning health system, and economic factors are all associated with maternal mortality particularly in SSA [4]. In particular, financial and opportunity costs are often cited as a demand side access barriers for women and families [5, 6].

There have been many demand side and supply side interventions to promote increased access and uptake of maternal health services [3, 4]. Interventions that increase antenatal care (ANC) visits before childbirth and skilled birth attendance (SBA) are widely known to improve maternal health outcomes [7, 8]. However, more use does not necessarily mean better outcomes due to quality of care provided at the facility [9]. Frequently, women in low-resource settings opt to deliver at home due to perceived cost or quality of care at a facility [10]. By improving the financial preparedness of a mother and family, the financial barrier for access to maternal health services and birth preparedness can be overcome.

Lack of financial preparedness for pregnancy can lead to adverse outcomes during childbirth [1]. Because a mother and her partner have not accounted for the costs of the pregnancy, they are less prepared if they encounter an emergency during childbirth. Promoting antenatal care visits or providing vouchers for transportation have been shown to increase skilled birth attendance and delivery in a hospital setting, but the effects are reduced once financial support is removed and is unsustainable [11]. Thus, more emphasis must be placed on increasing financial empowerment when it comes to spending money on healthcare.

Male heads of household are often the primary decision maker when it comes to family decisions in SSA, particularly decisions surrounding finances or healthcare [12]. Many studies have reported positive associations between male involvement in maternal healthcare and maternal health outcomes, such as male partner attendance at ANC, increased utilization of SBA, and reduction in post-partum depression [12–16]. Male involvement can also include financial support for transport or appointments in SSA [17]. Yet male involvement is still not commonplace, and financial barriers are often cited as a reason for not seeking maternal healthcare [5, 6]. Interventions that cluster other health services such as HIV testing with ANC or training healthcare workers to be more male-inclusive have shown positive effects in involving the male partner [18–20]. Most interventions are focused on education, such as teaching the husband about danger signs during a pregnancy so that they may seek early care or the timing of ANC appointments [15, 21, 22]. There is an opportunity to create a behaviorally informed intervention that encourages increased male involvement in maternal healthcare.

Behavioral science has had increasing influences in the field of public policy and public health, especially in terms of savings behavior. For example, behavioral “nudges” and “choice architecture” are cited as encouraging the public to change their behavior without extreme regulation, such as setting defaults on retirement savings accounts at workplaces [23]. Behavioral “insights” are defined as “an inductive approach to policy making that combines insights from psychology, cognitive science, and social science with empirically-tested results to discover how humans actually make choices” [24]. In SSA, behavioral approaches have been tested for motivating savings behavior and results have shown that physical reminders, such as a coin-shaped object where the participant tracks their own savings progress, have the most impact on savings behavior; text messages that sound like they are from their child had a marked improvement on savings behavior as well [25].

Financial savings interventions have also been used to improve health outcomes, although they are typically unsustainable in nature due to provision of vouchers or conditional cash transfer (CCT) programs [26]. For example, a study in India determined that a CCT program for increasing births in health facilities had a significant impact in the community [27]. A systematic review for CCTs to improve uptake of health interventions determined that although effective, the success of the CCT depends on the efficacy of the local service provision and infrastructure [28]. There is compelling evidence that well-designed financial interventions can improve health outcomes, but a reliance on external funds or external systems can reduce the impact.

Financial savings interventions can be adapted for encouraging individuals to save towards maternal health care costs. Approximately 12% of the world’s population spends at least 10% of their household budgets to pay for health care [29]. Even with increased public spending, service coverage of maternal, newborn, reproductive, and child healthcare is still low in low-income countries, and out of pocket expenditure is still high, especially in SSA [29]. Financial literacy overall is low in sub-Saharan Africa, and gender and power dynamics around spending decisions impact savings behavior [30]. Financial literacy interventions have limited impact and effect especially over the long term based on a systematic review, and recommendations are made to design savings devices with choice architecture and behavioral insights in mind [31].

Mobile money accounts are widely used in lieu of traditional banking in SSA [32]. Savings promotion trials generally increase savings rates in the region [33]. Training on financial literacy is not enough to encourage savings for maternal health care costs as the effectiveness of trainings on financial literacy is negligible [31]. Furthermore, individuals may still spend their savings on household expenses or other goods rather than maternal health care costs. There is limited evidence of savings interventions focused on health care [33].

In Uganda, the maternal mortality rate (MMR) stands at 336 per 100,000 live births [34]. The government contributes approximately 16% of the total cost of health expenditure with no social health insurance programs. Thus, Ugandan citizens typically pay a high out of pocket expenditure, which is associated with high financial risk. Furthermore, less than 0.7% of Uganda’s 42 million have adequate healthcare insurance coverage [34]. When considering the challenges in covering costs of pregnancy and delivery, there is an opportunity for couples to start saving earlier in preparation for a highly anticipated event. Small incremental amounts can add up and become future options, such as when couples would prefer to have a choice in selecting where to deliver their child to receive higher quality services [11]. Expectant mothers also might be expected to contribute up to 100,000 Ugandan Shillings (approximately USD 30) when delivering at a facility, which most mothers cannot afford due to the subsistence nature of their income earnings [11].

Male involvement in maternal healthcare in Uganda is in alignment with the findings about the SSA region in general, namely that positive outcomes are associated with increased male involvement but men are still not heavily involved [35]. Factors associated with increased attendance to ANC in one region were receiving information from a healthcare worker, knowledge of ANC services, and SBA at last delivery [36]. Interventions were focused on encouraging male attendance with HIV testing appointments or encouraging male-inclusive family planning services [20, 37]. Yet opinion leaders from key informant interviews suggested that without external financial aid, these interventions are not sustainable [38]. When men control the household finances and make decisions of households, finding a way to empower them to be involved on a voluntary and willing basis can lead to improved outcomes for maternal healthcare.

Out of 26 million mobile subscribers in 2020, approximately 7.4 million are using smartphones with the numbers increasing year over year [39]. Furthermore, mobile money is widely used in SSA with more than 9 million users registered in Uganda alone [40]. Thus, mobile money accounts are a suitable mechanism for encouraging savings in contexts where bank accessibility might be low to include the most vulnerable and hard-to-reach populations. Financial savings interventions in Uganda showed that incentives could increase the number of deposits and diversification of assets by families [41]. The problem is that pregnant women and families in Uganda are not financially prepared and empowered to access quality and timely maternal health care.

It is possible to see how savings interventions can be applied to the field of healthcare, and technology can also expand upon the possibilities for empowering people in Uganda. This study intends to apply behavioral designs through mobile money technology and short message service (SMS) text messages to encourage couples to save early in their pregnancy for birth preparation and potential emergencies. A local company registered in Uganda runs committed mobile money health savings accounts and will partner on recruiting participants and collecting data for the research.

### Objectives

The primary objective of this study is to assess the effectiveness of a behavioral intervention designed to encourage birth preparedness through financial savings for healthcare costs among pregnant women and their partners in Uganda. The study will also examine whether increased earmarked financial savings for healthcare costs lead to increased utilization of maternal health services and male involvement in maternal healthcare.

## Methods

### Study setting

The study will be conducted in Kampala and Wakiso districts in the central region of Uganda, a low-income country [42]. The study area was selected due to the high population density and varied housing patterns with urban, semi-urban, and rural areas. The population of the region is 3,504,498 (Kampala: 1,507,080; Wakiso: 1,997,418) [34]. The region has 2047 health facilities (Kampala: 1458; Wakiso 589) and 74.3% coverage of mobile phone ownership [34].

### Study design

We will conduct a randomized controlled trial (RCT) to test the effectiveness of the intervention comprised of a behaviorally informed mobile money health savings account on birth preparedness, maternal health service utilization, male involvement in maternal health, and savings amount towards healthcare costs. A dedicated mobile money health savings account will be provided by clinicPesa, a mobile money health savings company registered in Uganda. clinicPesa offers a commitment device for savings, where a client’s savings can only be spent on healthcare expenditures and not withdrawn for other purposes. The overall study flow chart is shown in Fig. 1. The schedule of the RCT is shown in the Standard Protocol Items: Recommendations for Intervention Trials (SPIRIT) figure (Fig. 2). The SPIRIT checklist is provided in Additional file 1.

**Fig. 1 Fig1:**
[figure not shown]
Study flow chart

**Fig. 2 Fig2:**
[figure not shown]
SPIRIT figure

### Sample size, eligibility, and recruitment

The minimum sample size for the RCT is 572 participants (286 in each arm). It was calculated using OpenEpi version 3. The power of the study was set at 80% and the significance level at 5%. A previous savings group research in a SSA region for maternal healthcare service utilization was used for assumptions [43]. Considering an approximate 20% dropout rate and sampling unit rounding, 700 participants will be recruited (350 participants in each arm).

To be eligible for joining in this study, participants should have the following characteristics: (1) 18–49 years old, (2) between 12–35 gestational weeks (pregnant female) OR partner of someone who is (male), (3) own a mobile phone, (4) has a registered Mobile Telephone Network (MTN) mobile money account, (5) willingness to enroll in clinicPesa’s health savings mobile money account. Participants are ineligible if their partner is known to already be participating in the study to avoid duplicating results of savings amounts; only one member per household may participate in the study.

Participants will be recruited and enrolled in person by clinicPesa at 77 public and private health facilities where clinicPesa operates. Five trained research assistants will approach male and female clients at the maternity ward of selected health facilities. The clients at the health facility will be offered an opportunity to enroll in the study when they sign up to join clinicPesa. In the case of a COVID-19 lockdown on movement, participants will be recruited through a phone query from clinicPesa’s registered user base. Users who sign up for clinicPesa agree to terms and conditions set by clinicPesa, which include the possibility of being offered to join studies to improve the product offered by clinicPesa.

### Randomization

A person who is not involved with any other study procedure (including recruitment, implementation of the intervention, and data analysis) will share a computer-generated randomized allocation table with clinicPesa at the beginning of the recruitment period, which will not be shared with the study recruitment team [44]. At the end of each recruiting day, the customer ID numbers of participants who agreed to join the study will be matched to the table to be assigned to either the control or the intervention group (1:1 randomization), and a study participant ID will be created to maintain participant anonymity within the study [32].

### Blinding

Participants will receive a description of the study during the informed consent process, but they will not be told which group they have been allocated to after enrollment. The study recruiters at the beginning of data collection and outcome assessors during final data collection will be blinded to the allocation. In addition, the data analyst will be blinded to the allocation of the participants until after the data analysis is complete.

### Intervention

The intervention consists of a basic mobile money health savings account as part of a Mamas Program offered by the local partner organization administering mobile money health savings accounts and additional behavioral designs to encourage savings for maternal health costs. The intervention was formulated using behavioral science approaches for promoting health savings towards the costs of maternal health care among pregnant women and their partners. The Mamas Program is a subset of the company’s clients that are registered as pregnant, and they receive additional reminders on ANC appointments, nutritional tips, and health tips about pregnancy. In the intervention group, participants receive the standard Mamas Program local company offering and messaging in addition to behavioral designs that encourage saving. The behavioral designs include “nudges” to encourage saving behavior; this will be done through reminder messages that sound like they are from their child, notifications about meeting their targets, and social norms notifications based on their savings rates and time in the intervention.

In the control group, participants receive the standard Mamas Program local company offering and messaging only. Both groups will have access to a mobile money health savings account as offered local company with the ability to deposit and withdraw health savings or set targets related to pregnancy for their savings goals, in addition to the Mamas Program messages for a healthy pregnancy.

It is assumed that the risk of contamination is low because participants are unlikely to share financial or account information with others, including any messages received from clinicPesa to an individual phone number. Participants can voluntarily withdraw from the study at any time.

### Outcomes

The primary outcome is level of birth preparedness and usage of maternal health services, assessed by the number of birth kits or items within birth kits purchased, antenatal care visits, skilled birth attendance by a doctor, nurse, midwife, and/or medical assistant or clinical officer, and delivery at a health facility, all based on recall by the participant; the amount of validated expenditure in participants’ clinicPesa accounts from the day of enrollment during the intervention period will also be assessed. The primary outcome will be measured by asking the participant during the end-line survey about their pregnancy and delivery experience.

Secondary outcomes include male involvement in maternal healthcare, measured by financial support, attendance to ANC, assisting with planning the delivery, and providing perceived emotional support to the mother, as well as total savings for healthcare, assessed using the validated amount of savings accrued in participants’ clinicPesa accounts from the day of enrollment plus any withdrawals for healthcare expenditures during the intervention period. The withdrawals will also be coded to determine if they were used for maternal health service costs, including transport, or other healthcare costs, such as birth preparedness kits, baby materials, or others. Deposits into the account will be coded by whether it was the mobile money account owner or another mobile money account (for example, a different family member saving into the account).

Male involvement in maternal healthcare will be assessed by measuring whether they provided financial support for clinicPesa or otherwise, attendance to ANC, and assisting with planning of the delivery, measured by an ad-hoc male involvement index [45]. Women will be queried about the perceived levels of involvement, and men will be queried about their level of involvement.

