### Data analysis

Background characteristics will be analyzed to determine that both the control and intervention groups were balanced and randomization was done correctly. The primary outcome of birth preparedness and maternal health utilization will be compared between the intervention and control groups. The mean total savings amounts of participants (regardless of expenditure) will be compared between the intervention and the control groups using T-tests for mean savings. Mixed-effect regression analysis will be performed to assess the effect of the intervention on the following outcomes: amount of money saved across the study period (plus withdrawals), birth preparedness, maternal health service utilization, male involvement in maternal healthcare, and utilization of money for pregnancy-related health costs (delivery, preparation, transportation, or other, if applicable). Logistic regression will be used to control for potential cluster effects. Weighting approach will be used to control for variation in probability of participants being included in the study across study recruitment sites (large facilities vs small facilities).

It is expected that after a participant enrolls in the study and is randomized, final savings data can be collected remotely even if the participant does not engage with the platform (i.e., does not save any money after enrollment) or complete the end-line survey. In this case, savings outcome data can still be collected. Attrition rates and reasons for dropout will be logged if possible. An intention to treat (ITT) analysis will be conducted, and a sensitivity analysis will be conducted for any missing data [48, 49]. The significance level will be set at 5%, and Stata version 13.1 will be used for analysis of the data set.

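### The primary outcome differs between the Abstract, Objectives, Outcomes and Data analysis sections, so the stated 5% level and 80% power attach to no identifiable hypothesis

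*Protocol article*

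**What the plan says.** Four sections of the protocol article describe the primary question, and a fifth sizes the trial for it.

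- **Abstract, Methods:** "The primary outcome is usage of maternal health services measured by level of birth preparedness and delivery at a health facility". Usage is the construct, and preparedness is one of its two measures.
- **Objectives:** the primary objective names birth preparedness. Utilization comes second: "The study will also examine whether increased earmarked financial savings for healthcare costs lead to increased utilization of maternal health services and male involvement".
- **Outcomes:** this section defines it as "level of birth preparedness and usage of maternal health services, assessed by the number of birth kits or items within birth kits purchased", followed by "antenatal care visits, skilled birth attendance by a doctor, nurse, midwife, and/or medical assistant or clinical officer, and delivery at a health facility", with every item recalled by the participant. After a semicolon the same sentence adds that "the amount of validated expenditure in participants’ clinicPesa accounts from the day of enrollment during the intervention period will also be assessed". The next sentence says the primary outcome is obtained by asking the participant in the end-line survey.
- **Data analysis:** a single primary outcome, made up of preparedness and utilization, is to be compared between arms. The list of regression outcomes then names the two separately. On error control it says "The significance level will be set at 5" percent.
- **Sample size, eligibility, and recruitment:** the minimum is 572 (286 per arm). "The power of the study was set at 80% and the significance level at 5" percent. On the effect assumed: "A previous savings group research in a SSA region for maternal healthcare service utilization was used for assumptions".

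**The concern.** The primary outcome decides what counts as success, and here it depends on which section is read. A later report could name preparedness, facility delivery or antenatal visits as primary and cite this protocol in support of each. An analysis plan can say how a primary outcome is tested, but it cannot make differing published definitions agree.

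Two quantities are at stake. The 5% level describes the trial's false-positive risk only if one test, or one rule joining several, is fixed in advance. The 80% power means something only for the variable whose rates entered the calculation, and that variable is not named.

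**Working it through.** **1. The sections side by side**

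| Section | Construct | Measures |
|---|---|---|
| Abstract | Usage | Preparedness; facility delivery |
| Objectives | Preparedness (utilization additional) | None named |
| Outcomes | Preparedness and usage | Kits or items; antenatal visits; skilled attendance; facility delivery; expenditure in an unclear role |
| Data analysis | One outcome, then two | Preparedness; utilization |

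The Abstract omits antenatal visits and skilled attendance, which Outcomes includes. The Objectives rank preparedness above utilization, while Outcomes and Data analysis put them level. The text does not describe a composite. The components in Outcomes mix counts (kits, visits) with yes/no events (attendance, facility delivery), and no score is given, although the same section names an index for the secondary outcome of male involvement.

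**2. The plan's own figure, 572**

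It cannot be reproduced, because the article gives no rates. Solving backwards with the two-proportion formula (two-sided 5% assumed, 80% power, 1:1), whole-percentage pairs that give exactly 286 per arm are:

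- without continuity correction: 19% v 29%, and 71% v 81%;
- with continuity correction: 39% v 51%, and 49% v 61%.

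These differ widely in control rate, so the sample size does not reveal which measure was powered.

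**3. False-positive chance if any one measure counts as success at 5%**

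For k independent tests the chance is 1 − 0.95^k.

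- One measure: 5%.
- Two (the Abstract's measures, or the two outcomes in Data analysis): 1 − 0.95² = 9.75%.
- Four (the recalled measures in Outcomes): 1 − 0.95⁴ = 18.5%.

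Positive correlation lowers the last figure. Simulating four equally correlated normal test statistics (500,000 draws; correlations assumed) gives 17.4% at 0.3, 15.6% at 0.5, 13.1% at 0.7 and 9.4% at 0.9.

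**4. Power if several primaries share an overall 5%**

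An effect with 80% power at two-sided 5% has an expected z of 1.9600 + 0.8416 = 2.8016. At the Bonferroni level, 286 per arm gives:

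- two primaries (0.025 each): Φ(2.8016 − 2.2414) = Φ(0.5602) = 71%;
- four primaries (0.0125 each): Φ(2.8016 − 2.4977) = Φ(0.3039) = 62%.

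Holm is never less powerful per test than Bonferroni, so these are floors for such an effect.

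**The case against.** The strongest reply is that this is a condensed article. A combination rule, a hierarchy or an alpha adjustment may sit in an analysis plan that is not shown, and its absence here is no finding. That stands, and it is why the point rests on sections that disagree and not on a missing adjustment.

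It can also be said that the Objectives state aims, not endpoints, and that their second sentence asks about a pathway from savings to use. That is fair in part. Setting the Objectives aside, the Abstract and Outcomes still list different measures, and Data analysis still moves from one outcome to two.

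Some stronger readings are tempting, but the documents do not support them:

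- **Five primary measures, each tested at 5%, with a false-positive rate near 23%** (1 − 0.95⁵ = 22.6%). Expenditure follows a semicolon as something also assessed. It comes from the account database, whereas the next sentence places the primary outcome in the end-line survey. The text sets one 5% level and nowhere says that each measure is tested at it or that any one suffices.
- **The sample size was built on the wrong outcome.** Utilization is part of the primary outcome in the Abstract, Outcomes and Data analysis, so utilization research is a consistent source. The gap is only that the powered measure is not named.
- **Facility delivery has little room to improve because recruitment is at health facilities.** The article gives no control rate, so any power figure for this would rest on assumed rates.
- **Preparedness should be the sole primary because the Objectives name it.** This sits badly with a sample size drawn from utilization research.

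**Conclusion.** The concern holds as an inconsistency in the definition of the primary outcome. At least the Abstract, Outcomes and Data analysis cannot all be followed as written, and the Objectives add a different ranking. As a result the 5% level and the 80% power belong to no identifiable hypothesis.

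The possible size is a false-positive chance of 9.75% for two measures and at most about 18.5% for the four recalled ones. These figures assume independent tests at 5% with any one counting as success. That rule is permitted by the text but not stated in it. Skilled attendance and facility delivery are probably correlated, so the real figure for four would be lower. An unseen multiplicity rule could bring it back to 5%, but it would not make the published definitions agree.

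**What to change.** State one primary outcome variable in identical words in the Abstract, Objectives, Outcomes and Data analysis. It should be the measure for which 572 was calculated, and the sample-size section should name it. List the remaining measures as secondary.

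State explicitly that account expenditure is not primary. It comes from the account database, not the end-line survey, and withdrawals for healthcare are already counted in the secondary outcome of total savings.

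If two or more primaries are kept, test them with Holm at an overall 5% and restate the power at 286 per arm: about 71% per test for two and about 62% for four, at the Bonferroni level, for an effect with 80% power at 5%.

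The cost is wording changes and possibly a less favourable stated power. No extra data or participants are needed.
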